## Abstract

**Background:** Three Cochrane reviews show that music therapy has a positive effect on schizophrenia concerning general functioning and positive/negative symptoms. This study aims to replicate these results in the Danish health system, a requirement for recommendation in guidelines from the Danish National Board of Health. **Methods:** The study is a randomized, controlled multi-site study, with a blinded design, aiming to include 90 participants who are 18–65 years in age, diagnosed according to ICD-10 with a schizophrenia diagnosis. The participants are randomized to one of two different music therapy activities for 25 weekly sessions. The study interventions are added to standard care. Outcome measures are rated at baseline, after 15 sessions and post therapy. A qualitative interview is performed as a one month follow up at the end of study. The primary intended outcome is a reduction in negative symptoms. The secondary intended outcome is progression in quality of life, alliance and psychosocial functioning. **Results:** As this study is still running, the results are not yet available. **Conclusion:** The study will investigate the direct effects of music therapy on negative symptoms as part of schizophrenia in a blinded, randomized trial. If proven effective, music therapy can be added to the small treatment armamentarium of effective therapies for negative symptoms in patients with schizophrenia.

## 1. Introduction

### 1.1. Background

The background for this study is based on three factors: (1) The treatment possibilities for the population under investigation are poor; (2) National Boards of Health in different countries recommend music therapy differently as a treatment possibility; (3) Music therapy has shown positive results in previous studies, where music therapy was added to standard care and compared to standard care alone. All three factors indicate that more evidence-based research is needed, with an active comparator as the second arm within the field.

The World Federation of Music Therapy (WFMT) produced the first common definition in 1996, and the most recent version from 2011 reads as follows: “Music therapy is the professional use of music and its elements as an intervention in medical, educational, and everyday environments with individuals, groups, families or communities who seek to optimize their quality of life and improve their physical, social, communicative, emotional, intellectual and spiritual health and wellbeing. Research, practice, education and clinical training in music therapy is based on professional standards according to cultural, social and political contexts” [1].

#### 1.1.1. Treatment Possibilities

Negative symptoms of schizophrenia have gone from being described as the primary feature of schizophrenia to being a secondary phenomenon [2]. Negative symptoms have been correlated with a lower quality of life, lower overall social and global functioning, as well as being associated with a decline in cognitive function [2]. Despite the correlation between negative symptoms and key areas of living, few studies have investigated possible treatments for the symptom cluster, and even fewer have showed an effect in the treatment thereof [3].

#### 1.1.2. Recommendation of Music Therapy for the Population

Previous studies have shown that music therapy can be an effective psychosocial treatment approach [4,5,6,7]. Based on these studies, art therapy, including music therapy, has since 2014 been recommended as a treatment method for patients diagnosed with schizophrenia in the National Institute for Health and Care Excellence (NICE) guidelines (UK) to promote recovery. It is stated that “...art therapies should be recommended to all people with psychosis or schizophrenia, particularly for the alleviation of negative symptoms.” [8].

The NICE guidelines justify their recommendation by stating that people with schizophrenia should be enabled to experience themselves differently, to be offered new ways of relating and expressing themselves and organizing their experiences into a satisfying aesthetic form ([8] p. 593).

The Royal Australian and New Zealand College of Psychiatry claimed in 2016 that the evidence from randomized, controlled trials in music therapy is inconclusive. Therefore, more studies investigating the effects of music therapy in this patient group are warranted before music therapy can be recommended as a standard treatment [9].

In Norway, the national treatment guidelines from (Helsedirektoratet) state that music therapy promotes wellbeing and that the treatment should start as early as possible in order to reduce negative symptoms (our translation) [10].

In Denmark, music therapy is not recommended in the treatment guidelines for schizophrenia in The Danish National Board of Health. It is recommended to “...develop and prove more effective psychosocial evidence-based treatment methods for this population” (our translation) ([11], p. 51).

This study is an attempt to contribute to the development of evidence-based treatment methods.

#### 1.1.3. Previous Positive Results

Three Cochrane reviews [4,6,7] have shown the positive effect of music therapy in patients diagnosed with schizophrenia, with an improvement of several general symptoms (among others, attention and motivation) and a reduction of negative symptoms. The main intervention methods of the studies have been (1) musical improvisation (where the music therapist plays a frame around the expression of the client and thus helps provide a musical structure where the client can feel like being a real part of interplay) and (2) song-writing (where the music therapist helps the client to structure texts made by the client and create a melody and musical accompaniment so they can sing the song, based on the text by the client, together. The studies were based on humanistic, resource-oriented and psychodynamic approaches. In all studies included, music therapy was added to standard care and compared to standard care alone. These reviews do not examine which elements in music therapy contribute to the overall effects observed. Qualitative research in the form of case studies has elucidated which elements in music therapy are assumed to be effective in the treatment. Musical elements, as well as elements in the therapeutic relationship seem to be crucial. Basic communication elements such as turn-taking in giving and taking a tone, a rhythm or a small melody are assumed to be effective in musical communication [12,13,14]. Additionally, joint musical expression at a very slow tempo, with as many repetitions as needed, are assumed to be effective in musical interplay [15,16]. These communication forms would not be as effective or meaningful in verbal communication. Furthermore, patients report it is meaningful to play or vocalize simultaneously with the therapist when the therapist follows the expression of the patient either in the form of imitation, matching or affective attunement [17]. These mechanisms are not so accessible in verbally mediated treatment.

Research on music and the brain has shown that the perception of music indicates that music and specifically music listening can positively affect brain chemistry. Among other effects, music listening can strongly affect and change activities in brain areas connected to emotional regulation and social response, such as the limbic and paralimbic structures [18]. This is in line with research showing that listening to preferred or selected music in the form of playlists can regulate emotions and moods in different ways [19,20]. Finally, qualitative research based on the analysis method of grounded theory in music therapy in patients diagnosed with schizophrenia, or those who present schizotypical disorders, has shown improvements in music listening, where the focus of the individual evokes inner imagery which can be shared verbally with a group of clients and the therapist [21]. Smaller studies, where mutual music improvisation among the therapist and client in a 1:1 setting was the applied intervention, also point at the importance of how the music therapist is consciously present in the therapeutic relationship when working with this population [22,23,24,25]. A general focus in these studies is on the therapist’s listening attitude and the therapist’s consciousness of being present in a disciplined state of being. Here, the therapist identifies with the patient’s state of being by consciously imitating and following the state of being of the patient, as expressed through musical interplay in the beginning. Gradually, with the right timing, the therapist can start to differ in musical expressions through small variations in musical expressions, gradually moving to a more inter-subjective state of being together, where both are engaged in the interplay as two subjects playing together [15,24,26,27].

Based on these factors, the aim of this study is to investigate whether music therapy can reduce negative symptoms in patients diagnosed with schizophrenia by using a randomized, controlled and blinded study design with an active comparator for the interventions. Furthermore, the study aims to examine if individual music therapy can increase the quality of life and establish progression in the alliance in the therapeutic relationship. Lastly, the study aims to investigate if the intervention can support and improve psychosocial functioning.

### 1.2. Hypothesis

We hypothesize that participants who are randomized to group I (the experimental group), when performed by educated and experienced music therapists offering multiple music therapy techniques adapted to the needs of the participant, will have a larger reduction in negative symptoms as measured by the clinical rating scale than participants who attend group II (the control group), where music is performed by non-music therapists, offering solely music listening. Furthermore, we hypothesize that participants randomized to group I will experience a larger increase in quality of life and in the progress of alliance building and psychosocial functioning as compared to group II.

## 2. Materials and Methods

### 2.1. A Randomized, Controlled and Blinded Study

The examination is a randomized, controlled, multi-site study, applying a blinded design including 25 sessions of manualized music therapy for the intervention group (group I) and 25 sessions of manualized music listening to selected playlists for the second arm with an active comparator (group II). The number of sessions is based on research concerning the dose response effect for music therapy for people with serious mental disturbances [28]. The arms of interventions are called intervention I and intervention II in the present study. Participants are rated at baseline, after 15 sessions and after 25 sessions post-therapy. At follow up (four weeks after post therapy at the end of study), a short, semi-structured interview will be performed with all participants. (See Table 1). Before baseline, all participants are informed (1) that they will be offered 25 sessions of music therapy, (2) that two different activities will be tested and compared (3) and that those performing the sessions are all referred to as therapists and are familiar with being together with people diagnosed with schizophrenia. (4) The participants will also be informed that recording of the musical activities might occur. All sessions will take place in the same equipped music therapy rooms. Intervention I is carried out by trained and experienced music therapists who are familiar with the population under examination, being carefully trained in and following a manual developed for this intervention in the study. Professional music therapists in Denmark all have a five-year full-time university BA/MA training, including several internship periods [29]. This training is based on a psychodynamic, humanistic and neuropsychological theoretical platform and is structured in three parallel running study tracks with equal weight through all five years. These tracks include an academic theoretical study track, a music-based improvisational methodological study track and a psychotherapeutic, self-experiential and clinical study track [29]. Due to the manual for Group I several music therapy methods and techniques can be applied including active methods (where the therapist and participant play or sing together, improvise, write songs or move to music), as well as receptive methods (where the therapist and participant listen to music together, either in the form of playlists selected by the music therapist, or in the form of participant-chosen or therapist-chosen music). The focus of the manual is about perspectives on the therapist’s way of being present and positions in the therapeutic relationship.

Intervention II is carried out by non-music therapists who are familiar with the population under examination, being carefully trained in and following a manual developed for this intervention in the study. Intervention II includes solely listening to specific playlists developed by music therapists. (This intervention is similar to one of the possible intervention methods in intervention I and thus both intervention forms can be called music therapy activities). All therapists performing intervention II are trained how to apply the playlists by a music therapist. Therapists performing intervention I have, as a premise, the possibility of applying multiple music therapy techniques, including the selected playlists. Their choice of techniques is currently adapted to the needs of the participants. Both manuals are developed according to unique, essential, possible and not-possible/proscribed principles for interventions and for the attitudes of the therapist in work with this population [30,31].

All participants included in the study and clinical personal accessing the participants will be blinded. Therapists, investigators and other researchers in the research steering group, including those who make the qualitative analysis as part of the data collection, will not be blinded. The participants will be rated with the scales and measures listed below in Section 2.4.

For analyzing musical communicative capacities, only those attending intervention I will additionally be subject to audio recordings of musical improvisations in sessions 1, 15 and 25 (if improvisation is performed in those sessions), as musical improvisation is not a part of intervention II. Finally, the therapy session reports about the participants’ experiences of music listening, experiences of music performance and level of initiative in verbalization will support the results as a whole.

The study involves two regions in Denmark: The North Jutland Region and the Capital Region. Within these regions, nine municipalities are involved. A cooperation agreement is signed for each region and for each of the municipalities.

### 2.2. Recruitment Processes

In the recruitment process, administrative and/or research heads of psychiatric centers will be contacted, and information meetings for daily contact persons for potential participants will be carried out at all centers that show interest in cooperation. Posters and leaflets will be spread throughout the centers and further information meetings will be offered if needed. These meetings often take place in two steps. The first step includes meeting with the contact person(s) alone and the second step is meeting with the contact person(s) and those diagnosed with schizophrenia, who have shown interest and who are supposed to be potential participants. After a trial period of five months, we learned that in each center, a contact person should be appointed to remind staff members to refer and to collect referrals and forward these with the needed information to the research coordinator. The coordinator receives the name, telephone number and e-mail address of the participant through secure mail. Both the potential participant and the contact person are permanently in contact with the coordinator (the same person for all participants in respectively the Region of North Jutland and the Region of the Capital) about potential questions around participation. The coordinator arranges for the inclusion screening procedure. At this first screening procedure, the project nurse asks the participant to sign an informed consent form in order to provide allowance to receive information of diagnosis, medical information and the hospitalization history of the single participant. If this is not possible, the client cannot be included in the study. The informed consent for taking part in the project as a whole is also signed at the first screening procedure after further information of the conditions involved in the study. After randomization, the coordinator will connect the participant and a relevant therapist, scheduling sessions at the equipped music therapy clinic room, located as close as possible to where the participant is living. If the participant is unable to take public transport, taxi tickets can be offered. The coordinator takes care that a time schedule for 25 sessions is made by the therapist and accepted by the participant. The therapist receives information of the name, telephone number and email address for both the participant and the contact person. The coordinator registers these sessions using Google Calendar. He is the person who will coordinate all screening procedures and interviews throughout the participation period of the single participant, due to the rules of the research design. All information about the single participant will be saved on a secure electronic drive.

The coordinator ensures that all relevant information is available and coordinates the inclusion screening procedure between the participants and the project nurse (screener). If the screening procedure results in inclusion, the participant is randomized by the Hospital Pharmacy, Region of Northern Jutland, which is not otherwise involved in the present study. A random variable block size randomization will be utilized in the study. The first session will take place no later than 14 days after the screening procedure to ensure the validity of the positive and negative syndrome scale (PANSS) evaluation conducted at the first screening. The study coordinator is responsible for assigning a relevant therapist, scheduling sessions and booking session rooms.

### 2.3. Inclusion and Exclusion Criteria

#### 2.3.1. Inclusion Criteria

The inclusion criteria are as follows:
(1)Age 18–65 years;(2)Diagnosis of schizophrenia by ICD-10 (F20);(3)PANSS negative subscale, minimum ≥4 on two of the following items, blurred affect (N1), emotional withdrawal (N2), poor contact (N3), passive apathetic social withdrawal (N4) and lack of spontaneity and flow in dialogues (N6).

#### 2.3.2. Exclusion Criteria

The exclusion criteria are as follows:(1)Diagnosis of schizophrenia less than two years ago;(2)Patients hospitalized less than three months ago due to their psychiatric illness;(3)PANSS positive subscale (P1–P7) > 28;(4)Patients who have had changes in psychotropic treatment during the last month;(5)Significant alcohol/drug abuse that may interfere with study participation, as judged by the investigator;(6)Presence of secondary negative symptoms, defined as:
(a)Calgary Depression Scale for Schizophrenia (CDSS) score >7 or;(b)Neurological side-effects UKU score >1 in the following items: Dystonia (2.2), rigidity (2.3), hypokinesia/akinesia (2.5), tremor (2.6) and motor akathisia or;(c)Sedative side-effect UKU item (1.3) or a sleepiness score >1;(d)Patients who have attended individual music therapy within the last 2 months.

#### 2.3.3. Treatment Schedule and Withdrawal Criteria

The treatment schedule is constructed to offer weekly sessions of 50 min of music therapy activities each 7 day +/− 1 day, resulting in a minimum of five days and a maximum of nine days between sessions. A session plan of 25 sessions is scheduled before the start of intervention and is accepted by the participant. If the participant fails to meet up to any of the scheduled sessions, with or without notice, the session will not be replaced. If the therapist cancels any of the scheduled sessions, replacements will be offered. The 25 scheduled sessions exclude holiday weeks. Participants will be withdrawn from the study as a whole if more than 30 days pass between two sessions or if the participant fails to turn up for more than five sessions. The participant will be reminded and warned by telephone if they fail to appear at three and four of the scheduled sessions, with a reminder of exclusion from further participation if a total of more than five lacking appearances occur. They will also be reminded if more than three weeks between scheduled sessions pass, often as part of a holiday, resulting in it being mandatory to attend the week after the holiday. Each therapist in the study is not allowed to plan for more than three combined weeks of holiday during each treatment schedule. Each time the participant fails to turn up without notice, the therapist will contact the participant to ensure the participant is safe and has planned not to attend this session. The participant will also be withdrawn from the study if they withdraw their informed consent. If hospitalization occurs during the study, the participant can continue in the study as long as the duration is short term (<5 days) and no change in medication has occurred.

Withdrawing from the study will in no way affect the individual participants’ treatment as usual.

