## 3. Results

### 3.1. Statistical Analysis

#### 3.1.1. Form of Statistical Analysis

As the study is still running, no final results are available. The results will be generated through statistical analysis where the endpoints from PANSS, BNSS and WHOQOL-BREF will be analyzed using mixed model effect analysis. Predictors for the response to the treatment will be performed by multiple logistic regression, using the severity of psychiatric disorders, timespan from diagnosis identified, psychotropic medication, PANSS score results and regional contra communal treatment as usual, as explanatory variables with a regression model being performed for each of the two randomized groups. The analysis will focus on identifying predictors of improvement of negative symptoms and change of quality of life, alliance and global functioning, as well as predictors for improvement connected to treatment (music therapy activities I or II). Both per protocol and intention-to-treat analyses will be performed. Intention to treat is defined as utilizing data from all participants, even if the single participant has not attended all 25 sessions. At the time of discontinuation from the study, a final assessment will be conducted, if possible. Participants will not be followed up on after this time point.

All tests will be applied double sided and the significance limit is defined as *p* < 0.05.

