## Figures and Tables

**Figure 1 medicines-06-00046-f001:**
[figure not shown]
Flow diagram of the experiment design. As the recruitment process is currently running, only the inclusion data can be presented.

**Table 1 medicines-06-00046-t001:** A SPIRIT diagram on screening procedures.

	Screening	Baseline		After Fifth before Sixth Offered Session	After Fifteenth before Sixteenth Offered Session			Less Than Eight Days after the Last Session Termination ^1^			Follow up 4–5 Weeks after Termination
No of visit	1	2		3	4			5			6
Performed by ^2^			MT/T	RP	PN	MT	RP	PN	MT	RP	RP
Information and consent	x										
Demographical data ^3^	x										x
Status of medicine	x	x ^4^			x			x			
History of abuse	x	x ^4^			x			x			
History of music therapy ^5^	x	x ^4^									
Inclusion and Randomization		X									
PANSS	x	x ^6^			x			x			
Brief Negative Symptom Scale (BNSS)	x	x ^4^			x			x			
WHOQOL	x	x ^4^			x			x			
Calgary Depression Scale for Schizophrenia (CDSS)	x	x ^4^			x			x			
Udvalg for Kliniske Undersøgelser (UKU), otherwise Task Force for Clinical Investigations	x	x ^4^			x			x			
Global Assessment of Functioning (GAF)	x	x ^4^									
Helping Alliance Questionnaire (HAQ-II)				x			x			x	
MIRS Only experimental group I			x			x			x		
Start of weekly interventions, groups I and II			x								
Start McGlashan rating after each intervention for experimental group I			x								
Termination of weekly interventions for groups I and II									x		
Interview											x

^1^ Is not performed if screening procedure after fifteenth session but before sixteenth offered session is performed ≤14 days earlier. ^2^ PN = rroject nurses; MT = music therapists group I, therapist group II; RP = research participant. ^3^ Sex, age, ethnicity, level of education, social and work situation. ^4^ Is not performed if performed by screening ≤28 days earlier. ^5^ Music therapy and other formalized music related offers other than trial treatment are registered. ^6^ Is not performed if positive and negative syndrome scale (PANSS) in screening is performed ≤14 days earlier.

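### Missing too many sessions ends study participation as well as the sessions, so the post-therapy PANSS negative score that the promised intention-to-treat analysis needs is not collected for those participants

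*Protocol article*

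**What the plan says.** Section 2.3.3 sets two attendance rules. The first is a gap rule: "Participants will be withdrawn from the study as a whole if more than 30 days pass between two sessions". The second is a count rule: "or if the participant fails to turn up for more than five sessions". Sessions missed by the participant are not made up: "If the participant fails to meet up to any of the scheduled sessions, with or without notice, the session will not be replaced". Under both rules the participant leaves the study, not only the sessions.

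Section 3.1.1 says what happens next. "At the time of discontinuation from the study, a final assessment will be conducted, if possible", and then "Participants will not be followed up on after this time point". The same section plans a mixed model for PANSS, with both per-protocol and intention-to-treat analyses: "Intention to treat is defined as utilizing data from all participants", including those who attended fewer than 25 sessions.

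Section 2.4 makes the primary outcome the change in the PANSS negative subscale. Section 2.1 places the ratings at baseline, after session 15 and after session 25. Table 1 times the final nurse rating (visit 5) as "Less Than Eight Days after the Last Session Termination". Its first footnote omits that visit when the session-15 rating is no more than 14 days old.

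**The concern.** An intention-to-treat comparison needs the outcome at the planned time for everyone randomised, whether or not they kept attending. Here the attendance rule itself switches off outcome collection. What remains for a withdrawn participant is a session-15 rating if they got that far, and an exit rating if one could be made. No analysis plan can restore scores that the protocol stops collecting.

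The people removed are unlikely to be a random subset. Entry (Section 2.3.1) requires a score of at least 4 on two items from a list that includes emotional withdrawal and passive social withdrawal, and Section 4.1.2 describes the population as poorly motivated to take part. It is a reasonable inference, though not stated in the article, that non-attendance is related to the primary outcome. The arms also differ in content and in who delivers them (Sections 2.1 and 1.2), so attendance may differ by arm. If both hold, a model that assumes missing at random may give a biased treatment contrast.

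**Working it through.** **1. What data a withdrawn participant contributes.** The table sets the rules side by side.

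| Rating | Completer | Withdrawn for non-attendance |
|---|---|---|
| Baseline PANSS | yes | yes |
| Session-15 PANSS | yes | only if still in the study |
| Post-therapy PANSS at the planned session-25 time | yes | no |
| Exit rating | not applicable | where feasible, at a variable time |

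The first footnote to Table 1 bears on timing. Sessions are weekly, so a completer's visit 5 falls about ten weeks after session 15 and the 14-day exemption cannot apply. It can apply only to someone who stops soon after session 15. Visit 5 therefore appears to double as the exit visit for early leavers, at a different exposure time from a completer's.

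**2. The plan's own figures (Section 2.7).** Effect size 0.6, two-sided alpha 0.05, power 0.80, two-sample t-test: the noncentral t gives 44.59 per group, which reproduces the stated 44.5. The allowance relevant here is the 10–20% drop-out.

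**3. How many the count rule might remove.** The article gives no no-show rate, so the rates p below are assumptions. Withdrawal needs 6 or more misses out of 25.

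- Independent misses: P(X ≥ 6), with X ~ Binomial(25, p), is 0.033 at p = 0.10 and 0.162 at p = 0.15.
- Between-person correlation ρ = 0.1: beta-binomial with a = p(1 − ρ)/ρ = 9p and b = 9(1 − p) gives 0.136 at p = 0.10 and 0.252 at p = 0.15.

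The count rule alone could therefore use little of the 10–20% allowance or exceed it. The gap rule and withdrawal for other reasons come on top.

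**4. When they would leave.** The share of those crossing the six-miss limit who do so within the first 15 sessions is P(≥ 6 of 15)/P(≥ 6 of 25).

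- Independent: 0.0022/0.033 = 7% at p = 0.10 and 0.0168/0.162 = 10% at p = 0.15.
- ρ = 0.1: 0.0408/0.136 = 30% and 0.0878/0.252 = 35%.

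Most people withdrawn under the count rule would already have a session-15 rating. This does not cover early gaps of over 30 days or voluntary exits.

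**5. Form of the bias.** For a simple contrast of those who stay, with no true effect, bias = (difference in withdrawal rate) × (outcome gap between leavers and stayers). Assuming 10% against 20% withdrawal and a gap of 0.5 to 1.0 SD, this is 0.10 × 0.5 = 0.05 SD to 0.10 × 1.0 = 0.10 SD. With equal withdrawal and an equal gap in both arms it is zero. The planned mixed model is not this contrast, so these values show the mechanism and do not estimate the bias in the trial.

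**The case against.** The strongest reply is that the plan is a mixed model, not a completers' analysis. It uses the session-15 and exit ratings and is valid under missing at random. Step 4 supports this, since most people crossing the six-miss limit would have a session-15 score. This reply stands as far as it goes. It narrows the problem to data missing not at random, which is the mechanism of concern here.

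Several stronger readings are tempting but unsupported:

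- *The analysis amounts to completers plus last value carried forward.* Nothing in the article plans carry-forward. How an exit rating is time-coded is commonly left to the analysis plan, which is not shown.
- *Very large losses.* The same binomial gives 38% at a 20% no-show rate and 62% at 25%. Those rates fit poorly with the Conclusions, which report that many participants attended every session. With independent misses, full attendance would be 0.80^25 = 0.4% and 0.75^25 = 0.1%. The article also describes telephone warnings, taxi tickets and cooperation with staff and relatives.
- *Non-attendance is the symptom itself.* This is plausible but inferred. Section 2.3.3 names holidays as one cause of gaps.
- *The primary endpoint has no PANSS rating*, because Section 2.1 describes the follow-up as "four weeks after post therapy at the end of study". Sections 2.1 and 4.1 show that the last PANSS is post-therapy and that the follow-up is an interview only, so this is loose wording.

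It is also fair to say that an amendment comes late: 47 of the intended 60 had been included by November 2018.

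**Conclusion.** The point holds as a design weakness, rated should-fix. The withdrawal rule and the end of follow-up are explicit, and together they leave the post-therapy PANSS negative score uncollected for people whom the intention-to-treat analysis claims to include. The mixed model reduces the gap but does not close it, because it relies on missing at random.

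A reader might infer that randomisation no longer protects the comparison. The document does not support that. Bias requires withdrawal or outcome gaps to differ between arms in a way that the observed ratings do not explain, and neither the size nor the direction can be computed from what is given. The illustrative 3% to 16% (or 14% to 25% with correlation 0.1) rests wholly on assumed no-show rates of 10% to 15%. It shows only that the count rule could take up a material part of the 10–20% allowance or more.

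**What to change.** Leave the rule for ending the sessions as it is, and separate it from leaving the study:

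- Invite every randomised participant who still consents to data collection to the existing session-15 and post-therapy ratings, at the calendar dates of their original session plan. Section 2.3.3 already requires that plan before the first session.
- Enter those ratings in the intention-to-treat mixed model.
- Analyse any exit rating at its actual date, not as the session-25 visit.
- Add a sensitivity analysis for data missing not at random, for example by shifting the assumed outcomes of withdrawn participants over a stated range, separately by arm.

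The cost is a short amendment and up to two nurse visits of a kind already in the schedule for each withdrawn participant. At the stated drop-out that is 0.10 × 60 = 6 to 0.20 × 60 = 12 people. Some will decline. The change helps mainly current and later participants, so follow-up rules will differ over the course of the trial and the report should say so. For those already withdrawn whose planned dates have passed, only the sensitivity analysis helps.
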